# Does a pulmonary rehabilitation based ERAS program (PREP) affect pulmonary complication incidence, pulmonary function and quality of life after lung cancer surgery? Study protocol for a multicenter randomized controlled trial

**DOI:** 10.1186/s12890-020-1073-6

**Published:** 2020-02-18

**Keywords:** Pulmonary rehabilitation, Lung cancer surgery, Enhanced recovery after surgery, Post-operative complication incidence, Pulmonary function, Health-related quality of life, Multicenter randomized controlled trial

## Abstract

**Background:**

Lung cancer surgery is associated with a high incidence of postoperative pulmonary complications (PPCs). Preliminary evidence suggests that ERAS processes can reduce overall incidence of PPCs as short- and long-term recovery improved by supporting units to adopt evidence-based care. However, the evidence is inconclusive due to insufficient high-level studies in this research field. No well-designed, adequately powered, randomized controlled trials (RCTs) have investigated the effects of pulmonary rehabilitation based ERAS program (PREP) on post-operative pulmonary complications, pulmonary function, and health related quality of life following lung cancer surgery.

**Methods:**

The PREP trial is a pragmatic, investigator-initiated, multi-center, randomized controlled, parallel group, clinical trial. Five hundred patients scheduled for minimally invasive pulmonary resection at six hospitals in China will be randomized with concealed allocation to receive either i) a pre-operative assessment and an information booklet or ii) a pre-operative assessment, an information booklet, plus an additional education, a 30-min pulmonary rehabilitation training session and the post-operative pulmonary rehabilitation program. The primary outcome is incidence of PPCs defined with the Melbourne Group Scale diagnostic scoring tool. Secondary outcomes include incidence of cardiopulmonary and other complications, pulmonary function, cardiopulmonary endurance, muscle strength, activity level, health-related quality of life (HRQoL), pre- and post-operative hospital length of stay (LOS), and total hospital LOS.

**Discussion:**

The PREP trial is designed to verify the hypothesis that pulmonary rehabilitation based ERAS program reduces incidence of PPCs and improves pulmonary function and HRQoL in patients following lung cancer surgery. This trial will furthermore contribute significantly to the limited knowledge about the pulmonary rehabilitation based ERAS program following lung cancer surgery, and may thereby form the basis of future recommendations in the surgical community.

**Trial registration:**

Chinese Clinical Trial Registry: ChiCTR1900024646, 21 July 2019.

## Background

Minimally invasive pulmonary resection is currently the most frequent and effective intervention for lung cancer. However, lung cancer surgery is associated with a high incidence of postoperative pulmonary complications (PPCs) with a reported incidence of 15.8–31.7% based on large sample studies [1, 2]. This is higher than the incidence for other major surgical procedures such as orthopedic surgery (0.3–3.6%), cardiac surgery (1.5–28.4%), upper and lower abdominal surgery (1.8–23.7% and 1.9–4.3%) [3–16]. The term PPC is defined as clinically significant respiratory complication or dysfunction requiring medical and rehabilitation intervention. Although the causes of PPCs are multifactorial, surgical procedure induced systemic inflammatory and catabolic response have been proposed as major contributing factors in the development of PPCs, leading to the changes in the short-term activity ability, and long-term health-related quality of life (HRQoL) and mortality after lung cancer surgery [17].

Enhanced Recovery After Surgery (ERAS) practices improve the opportunity for rapid, uncomplicated recovery after surgery with both short- and long-term benefits for patients [18]. Data suggest that complication rates can be reduced by 10–50% or more with supporting units to adopt evidence-based EARS care [19–22]. Further data also showed that not only were overall complications reduced, but the most severe complications, which resulted in decreased rates of reoperation or admission to the intensive care unit (ICU) as mortality improved [20, 23]. Recently, ERAS principles have been applied across most surgical specialties. After the ERAS Society was formed in 2010, the Society published a series of guidelines and recommendations on colonic resection, rectal resection and pancreaticoduodenectomy in 2012, cystectomy and gastric resection in 2015, bariatric surgery, liver resection, and head and neck cancer surgery in 2016, breast reconstruction in 2017 [18]. Nonetheless, the ERAS guideline for thoracic surgery is still under production, revealing that there is a paucity of quality resear on adopting these principles in this field. To date, no multicenter randomized controlled trials (RCTs) support the provision of pulmonary rehabilitation based ERAS program (PREP) on reducing PPCs and shortening recovery time, which translate to a substantial improvement of quality of life (QoL) following the ERAS principle. Considering the high incidence of PPCs following lung cancer surgery, ongoing innovation must move from guessing to knowing the outcomes though adequately powered research. Therefore, a well-designed, multicenter RCT is needed to determine the clinical effects of pulmonary rehabilitation based ERAS program on reducing incidence of PPCs following lung cancer surgery. The results of the current trial may fill the blank of applying ERAS program in this field and may contribute to the construction of ERAS guideline on lung cancer surgery.

### Trial objectives

The primary objective of the PREP trial is to investigate the effects of PREP, specifically pre-operative education combined with post-operative pulmonary rehabilitation, on the incidence of PPCs following lung cancer surgery. Secondary objectives are to estimate the effects of PREP on cardiopulmonary complications, other complications pulmonary function, cardiopulmonary endurance, muscle strength, activity level and HRQoL, pre-operative and post-operative hospital LOS, and total hospital LOS.

## Methods/design

### Trial design

The PREP trial is a pragmatic, investigator-initiated, multi-center, randomized controlled, parallel group, clinical trial. Table 1 shows the overview of the trial methods and design.

**Table 1 Tab1:** World Health Organization (WHO) Trial Registration Data Set for PREP trial

Data category	Information
Primary registry and trial identifying number	Chinese Clinical Trial Registry number: ChiCTR1900024646
Date of registration in primary registry	21/07/2019
Secondary identifying numbers	N/A
Trial protocol version	Version 1
Source(s) of monetary or material support	Clinical research grant from the Department of Rehabilitation Medicine in the First Affiliated Hospital of Nanjing Medical University (1,200,000 CNY)
Primary sponsor	N/A
Secondary sponsor	N/A
Contact for public queries	XL, [contact]
Contact for scientific queries	XL, [contact]
Public title	Pre- and post-operative physiotherapy for the prevention of complications and the improvement of pulmonary function and quality of life after lung cancer surgery: a multi-center randomized controlled trial
Scientific title	Pre- and post-operative physiotherapy for the prevention of complications and the improvement of pulmonary function and quality of life after lung cancer surgery: a multi-center randomized controlled trial
Countries of recruitment	China
Health condition(s) or problem(s) studied	Complication incidence, pulmonary function and quality of life following lung cancer surgery
Intervention(s)	Active comparator: Education booklet combined with a 30-min pre-operative pulmonary rehabilitation training session and daily post-operative pulmonary rehabilitation
	Placebo comparator: Education booklet
Key inclusion and exclusion criteria	Ages eligible for study: 18-80 yr
	Sexes eligible for study: both
	Accepts health volunteers: No
	Inclusion criteria: (i) diagnose with lung cancer through medical history, clinical symptoms, radiographic assessment and pathological results; (ii) Karnfsky ≥60 and estimated survival period > 6 months; (iii) to undergo minimally invasive lung cancer surgery (namely the video-assisted thoracoscopic surgery, VATS); (iv) with normal cognitive function and being able to cooperate with the rehab training; (v) the participation in the PREP trial and sign the informed consent form
	Exclusion criteria: (i) refuse the randomization; (ii) with severe limb dysfunction or systemic diseases and being unable to cooperate with the rehab training; (iii) with severe cognitive and mental dysfunctions; (iv) participated in other trials previously
Study type	Type: Pragmatic, investigator-initiated, multi-center, randomized controlled, parallel group, clinical trial
	Allocation: Concealed randomization
	Intervention model: Parallel assignment
	Masking: Assessor, surgeon, data analyst, and statistician blinded
	Primary purpose: Prevention and improvement
	Phase: Phase III
Date of first enrolment	1/8/2019
Target sample size	500
Recruitment status	Recruiting
Primary outcome(s)	Post-operative pulmonary complications incidence
Key secondary outcomes	Pulmonary function, six-minute walking test, health-related quality of life

### Trial setting

The six participating centers from different regions generally represent the whole picture of China. The First Affiliated Hospital of Nanjing Medical University (Nanjing in Eastern China) is a 3700-bed metropolitan, primary referral hospital; the Second Affiliated Hospital of Hainan Medical University (Haikou in Southern China) is a 2100-bed coastal, primary referral hospital; Nanjing Drum Tower Hospital, the Affiliated Hospital of Nanjing University Medical School, (Nanjing in Eastern China) is a 3000-bed metropolitan, primary referral hospital; the First Affiliated Hospital of Zhengzhou University (Zhengzhou in central China) is a 7000-bed inner-regional, primary referral hospital; Shenzhen Dapeng New District Nan’ao People’s Hospital (Shenzhen in Southern China) is a 300-bed coastal, secondary referral hospital and Taizhou Enze Medical Center, Enze Hospital (Taizhou in Eastern China) is a 1000-bed medium-sized, primary referral hospital. The First Affiliated Hospital of Nanjing Medical University and the Second Affiliated Hospital of Hainan Medical University have implemented Enhanced Recovery After Surgery (ERAS) guidelines to all surgical units. Relevant medical staff from the six participating centers have been trained with the standardized procedure of enrollment, randomization, rehabilitation intervention, assessment and data collection at the kick-off meeting.

### Eligibility criteria

The target population for this study are those who met the consolidated inclusion criteria: (i) diagnose with lung cancer through medical history, clinical symptoms, radiographic assessment and pathological results; (ii) aged 18–80; (iii) Karnfsky ≥60 and estimated survival period > 6 months; (iv) to undergo minimally invasive lung cancer surgery (namely the video-assisted thoracoscopic surgery, VATS); (v) with normal cognitive function and being able to cooperate with the rehab training; (vi) the participation in the PREP trial and sign the consent form [24–27].

The exclusion criteria are as follows: (i) refuse the randomization; (ii) with severe limb dysfunction or systemic diseases and being unable to cooperate with the rehab training; (iii) with severe cognitive and mental dysfunctions; (iv) participated in other trials previously [28–30].

The institutional review board in the First Affiliated Hospital of Nanjing Medical University has approved the trial with the protocol reference of 2019-SR-360. The trial will be conducted in accordance with the Declaration of Helsinki and was registered on 21 July 2019 at the Chinese Clinical Trial Registry (http://www.chictr.org.cn): ChiCTR1900024646.

### Recruitment, randomization and allocation

Eligible patients potentially undergoing lung cancer surgery at the participating centers will be assessed by a multi-disciplinary team consisting of a registered nurse, anesthetist, and surgeon from the admitting surgical team one to 2 weeks prior to their operation. Face-to-face pre-operative education in terms of the surgical process, pain management, postoperative drips and drains, and expected recovery process will be delivered.

Six sets of allocation sequence is determined by a web-based computer generated (http://www.randomizer.org/) random number table (Odd = intervention, Even = control). These tables are then sealed in six sets of 150 sequentially numbered (1 to 150) opaque envelopes, each containing an allocation card, prepared by a medical staff masked to the trial [31].

Eligible patients will be provided with a sheet including trial information about the randomization process, the discrepant rehabilitation plans, the surgical process, pain management, postoperative drips and drains, and expected recovery process. Those agreeing will sign a consent form as required by the ethics committee and in accordance with the Declaration of Helsinki.

Once informed consent form has been signed, patients will be allocated to one of the two experimental groups, by opening the sequentially numbered opaque envelopes, to receive 1) a pre-operative assessment and an information booklet (control) or 2) a pre-operative assessment, an information booklet, plus an additional education, a 30-min pulmonary rehabilitation training session and the post-operative pulmonary rehabilitation program (intervention). A trial participation sticker containing patient details will be attached on the opened envelope which will be filed securely with the informed consent form. Figure 1 demonstrates the overview of the recruitment, randomization and allocation based on the CONSORT principle.

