### Blinding

Trial assistants and clinic nurses at each study center will be masked to the group allocation pre- and post-operatively. Due to the nature of the intervention, the patients cannot be blinded to the group allocation. In each center, two groups of physiotherapists will be assigned to the intervention group or the control group to maximally avoid performance bias. The trial administrators at each study center who are aware of the group allocation will assign patients in the intervention group to one medical unit whereas the control group to the other unit. The medical staff including assessors, surgeons, data analysts, and statisticians will be blinded to the group allocation.

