### Data management

Standardized case report forms (CRF) have been developed specifically for the trial. Completed forms are periodically sent by the participating centers to the coordinating center (the First Affiliated Hospital of Nanjing Medical University) for verification and data entry though a secured website. Local policy and national data protection guidance will be followed with study data anonymously recorded on a bespoke trial database using unique study identification numbers.

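### The patient is tied to an allocation only after the envelope has been opened, so an opened card could be re-used without leaving a gap in the envelope series

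*Protocol article*

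**What the plan says.** All of the following is in the protocol article.

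- **Envelopes.** Allocation cards are held in "six sets of 150 sequentially numbered (1 to 150) opaque envelopes", one set for each centre. They are prepared by someone masked to the trial (Recruitment, randomization and allocation).
- **Order of steps.** "Once informed consent form has been signed, patients will be allocated to one of the two experimental groups, by opening the sequentially numbered opaque envelopes".
- **Identification.** "A trial participation sticker containing patient details will be attached on the opened envelope". The labelled envelope is then stored with the consent form.
- **Knowledge of the arms.** The information sheet given before consent describes both rehabilitation plans (same section). Patients cannot be blinded, and "The trial administrators at each study center who are aware of the group allocation will assign patients" to a different medical unit for each arm (Blinding).
- **Analysis.** All outcomes are to be compared by intention to treat (Statistical methods).
- **Eligibility.** One of the exclusion criteria is "refuse the randomization" (Eligibility criteria).

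The article does not say who opens the envelope, or at what moment a patient counts as randomised.

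**The concern.** Concealment by envelope has two parts. Nobody should be able to foresee the next card, and nobody should be able to change who receives a card once it has been seen. Opaque envelopes in numbered order serve the first part. The second needs an irrevocable link between patient and envelope before the arm is revealed, and here the link is made afterwards.

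The temptation is realistic in this trial. The control arm receives a booklet and no physiotherapist guidance, while the other arm receives supervised training before and after surgery. Patients know this when they consent. A disappointed patient, or staff with a view on who would benefit, could act in the interval between opening and labelling.

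What is at stake is comparability of the arms for the primary outcome, pulmonary complications within 14 days. The Discussion relies on effective randomization and blinding to balance factors that were deliberately left uncontrolled, such as timing of ambulation and analgesia. If selection occurred after the arm was known, no planned analysis could identify or undo it.

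**Working it through.** There is no plan figure to reproduce here. The check is to follow the stated steps and ask what the trial file would show in each case. Let patient A consent first and patient B next, with envelope *n* next in line.

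| Case | What happens | What the file shows under the stated order |
|---|---|---|
| 1. As intended | A consents, *n* is opened, A's sticker goes on *n* | Complete series; every consent has an envelope |
| 2. Envelope discarded | *n* is opened for A and thrown away; A receives *n*+1 | Number *n* is missing, so it is detectable |
| 3. Card re-used, A left out | *n* is opened for A, who is not registered; B's sticker goes on *n* | Complete series; A's consent has no envelope |
| 4. Cards exchanged | *n* is opened for A; B's sticker goes on *n*; A receives *n*+1 | Complete series; every consent has an envelope; consent order and envelope order disagree |

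1. Sequential numbering catches case 2. It does not catch cases 3 and 4, because no number goes missing.
2. Filing the envelope with the consent form leaves a trace in case 3, namely a consent without an envelope. That trace is ambiguous: a patient who consented and dropped out before any envelope was opened would leave the same record.
3. Case 4 shows only if consent dates are compared with envelope numbers, and then only if the two consents can be put in order.
4. Intention to treat keeps a registered patient in the assigned arm. In case 3, A was never registered, so A is outside the analysis set. In case 4, both patients are analysed in the arms on their stickers, which are not the arms that chance gave them.
5. If A's study ID, date and time are on envelope *n* and in a log before opening, cases 3 and 4 both require an altered envelope and an altered log entry. Case 3 becomes a randomised patient without data, which is visible and belongs in the intention-to-treat set.

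**How much of the trial could still benefit.** Trial status gives a start on 1 August 2019 and an expected 15 to 20 patients a month. The article appeared on 18 February 2020, about 6.5 months later. If that rate was met (an assumption), 6.5 × 15 ≈ 98 to 6.5 × 20 = 130 patients had been enrolled. That leaves about 370 to 400 of the 500 still to be allocated.

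**The case against.** The strongest reply is that the procedure already contains the usual safeguards. Envelopes are opaque and numbered, consent comes before opening, and the labelled envelope is filed with the consent form. The next allocation is therefore unknown when a patient agrees to take part, and a patient dropped after opening leaves a signed form behind. This stands in part. It would be wrong to say that re-use leaves no trace, or that concealment and intention to treat are defeated. What remains is that the trace is weak and the order of steps is easily improved. That an article condenses the full protocol does not answer the point, because the article states this order itself.

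A reader might infer two stronger points that the article does not support.

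- **That the exclusion criterion "refuse the randomization" permits removal after an unwelcome allocation.** It is an eligibility criterion. The described order is eligibility, information about both plans, consent, then the envelope. Someone who refuses randomization does not reach an envelope, and intention to treat is stated for all outcomes.
- **That the lists are unblocked and that this is a defect.** The article says only that the sequence comes from a "random number table (Odd = intervention, Even = control" rule. That tells us how numbers map to arms, not whether the draw was restricted, and block details are commonly left to the full protocol. Even under simple randomization there is no bias. With 500 patients the 95% range for one arm is 228 to 272. Power for 20% against 10% is 88.2% at 250 per arm and 87.7% at the less favourable limit, a loss of about half a percentage point at most. Blocks would also make allocations somewhat easier to predict where site administrators know earlier ones.

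**Conclusion.** The point holds in a narrow form and is minor. As written, the procedure identifies the patient on the envelope only once the arm is visible. A card could then be redirected, or a patient left unregistered, with the envelope series intact. This rests on the article's own sequence of steps and on the absence of any described earlier link. A pre-opening record in the full protocol, which is not shown, would settle it.

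No size can be derived from the documents. A reader might want to quote a bias. If *k* patients were exchanged for *k* others whose complication risk differs by *d*, with 250 per arm, the spurious difference would be 2 × *k* × *d* / 250. With assumed risks of 40% and 15% (*d* = 0.25):

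- *k* = 0 gives 0;
- *k* = 1 gives 2 × 1 × 0.25 / 250 = 0.2 percentage points;
- *k* = 10 gives 2 × 10 × 0.25 / 250 = 2 percentage points, against the 10-point target in Sample size calculation.

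Neither *k* nor *d* comes from the article, so these figures are not evidence of bias. The reason to act is that the weakness costs almost nothing to close and could not be repaired in the analysis.

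**What to change.** Replace the labelling sentence with a rule in this order: (a) consent is signed; (b) the study ID, date and time are written on the next sealed envelope; (c) the same details are entered in an allocation log; (d) the envelope is opened. State that the patient counts as randomised from the log entry and stays in the intention-to-treat set whatever happens afterwards.

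The log could use the system that already exists "for verification and data entry though a secured website". The article describes it for forms that are sent in periodically, so the team should confirm that it can take an entry from a site at the moment of allocation. If it cannot, a numbered log at each centre, copied to the coordinating centre, would serve.

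For patients already enrolled, compare signed consent forms with opened envelopes at each centre once, by count and by date order, and explain any consent without an envelope.

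The cost is one log entry per patient and one revised procedural sentence. No extra patients are needed, and the allocation lists and the treatments stay as they are.
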